## ENDPOINTS

3

The general purpose of this study is to determine the effectiveness, comfort, and experience of the patient catheterized with T‐Control® compared with patients with a conventional Foley catheter, by evaluating patients with long‐term urinary catheters.

Primary endpoints are as follows:
To analyse, through qualitative techniques, the comfort and acceptability of the T‐Control® device for the patient framed in the course of the disease, identifying preferences and training and information needs for the use of the device; andTo analyse and compare the degree of satisfaction and levels of self‐perceived health‐related quality of life of patients with both types of catheters.

Secondary endpoints are as follows:
To assess the preliminary effectiveness of T‐Control versus a common Foley catheter, by comparing the magnitude and rate of infections (both symptomatic and asymptomatic) due to the catheter among long‐term catheterized patients. Additionally, evaluate the effectiveness of T‐Control by comparing the days free of infection on the 28th day after catheterization;To compare the indication of antibiotic treatments associated with catheter use between the conventional Foley‐type catheter and the T‐Control device;To determine the biofilm formed in the catheters and identify the microorganisms that form this to evaluate its relationship with the onset of symptomatic and asymptomatic infections as well as different adverse events;To compare the number and relevance of adverse events related to bladder catheterization between T‐Control and the traditional Foley catheter;To assess the preliminary cost‐effectiveness of T‐Control versus the traditional Foley catheter from the public healthcare services perspective; andTo measure and compare the level of satisfaction and workload perceived of health professionals with both types of catheterization by means of a questionnaire at the end of the study.

## ELIGIBILITY CRITERIA

4

Patient inclusion criteria are as follows: (1) men or women aged >18 years; (2) patients who require a change of bladder catheter; (3) absence of symptoms compatible with infection; (4) indication of bladder catheterization for 4 weeks; (5) maintained cognitive and physical capacity for self‐monitoring of the catheter valve; and (6) signed consent agreement.

Patient exclusion criteria are as follows: (1) symptoms of current UTI; (2) use of current antibiotic treatment or in the 2 weeks prior to inclusion in the study; (3) patients with malformations in the urinary tract; (4) immunocompromised patients; (5) patients with urological cancer; (6) patients who require continuous urine drainage (in the case of patients in the study arm) or hourly urine output measurement; (7) catheter insertion requiring more than one attempt; and (8) inability to read and understand Spanish.

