### Recruitment

2.2

Patients eligible to participate will be identified by the health professionals responsible for the study. All those patients who require a change of long‐term bladder catheter will be invited to participate and will be interviewed in an initial visit, where the inclusion and exclusion criteria will be checked, and the patients or their relative/caregiver (if necessary) will receive information about the study, will be invited to participate in the study, and will request their consent agreement, including the subject on the study's registration sheet.

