### Random assignment

2.3

Participants will be assigned 1:1 to one of the two trial arms of the quantitative study by a local research team member using a centralized computerized randomization system (RAND2 software, The MathWorks Inc, Natick, USA, administered by the data management team, depending on the contract research organization [CRO]).

The blinded allocation sequence is concealed by the use of a centralized computerized randomization system. The personnel responsible for catheter insertion will enrol subjects on the randomization system.

The patient's identifying number will be consecutively assigned, and inclusion in the intervention group or control group will be carried out through the randomized numerical distribution generated by a random online generator.

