### Study procedures

5.2

The flowchart in Figure 1 describes the participant timeline throughout the study. The catheter will be inserted by the research staff after obtaining informed consent (Data S8), and the inclusion and randomization of the participants. The healthcare professional who inserts the catheter must have experience in bladder catheterization. Professionals without sufficient experience in catheterization involved in the study will receive specific training prior to the start of the study. In addition, the research staff will receive specific training on the device prior to the start of the study (Data S1). All the staff involved in the study will have access to the user instructions at any time.

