### Analysis plan

5.7

A statistical analysis plan will document the scheduled analysis, to be finalized before the data lock. The final analysis will take place after full recruitment and follow‐up, at the end of the study.

The analysis population will consist of all patients who meet the selection criteria and are randomized. All patients included in the study and excluded from the analysis will be listed along with their reason for exclusion. Additionally, additional analysis will be performed on patients who complete 4 weeks with the catheter. Subjects who withdraw from the study for any reason after signing the informed consent will not be replaced. No imputation will be made for missing data.

Descriptive statistics will be carried out on the variables under study, using frequencies and percentages for qualitative variables and mean with standard deviation for quantitative variables that follow a normal distribution; otherwise, the median and interquartile ranges will be calculated.

A bivariate analysis will be carried out between the control–study groups with respect to the independent variables to know the comparability of the groups using the Chi square tests for qualitative variables and for the quantitative variables *t*‐Student or Mann–Whitney U, depending on the normality of the sample. All are under a 95% confidence interval and considering statistically significant results with a *p*‐value < 0.005.

In the event that the results are discordant, deviations and/or violations of the protocol will be analysed. For all analyses, the SPSS 24.0 statistical package^31^ will be used and will be carried out by a person who will not know if the patients have been in the intervention or control group.

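### Exclusion criterion 6 bars patients needing continuous drainage from the T-Control arm only; it cannot be applied before concealed allocation and makes the analysed arms non-comparable

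*Protocol article*

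**What the plan says.** All references are to the protocol article.

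- **Section 4 (Eligibility criteria), exclusion 6:** "patients who require continuous urine drainage (in the case of patients in the study arm) or hourly urine output measurement". The arm qualifier is attached to continuous drainage. Hourly output measurement carries none.
- **Section 2.2 (Recruitment):** candidates "will be interviewed in an initial visit, where the inclusion and exclusion criteria will be checked".
- **Section 2.3 (Random assignment):** "Participants will be assigned 1:1 to one of the two trial arms of the quantitative study". On concealment: "The blinded allocation sequence is concealed by the use of a centralized computerized randomization system". On who enrols: "The personnel responsible for catheter insertion will enrol subjects on the randomization system".
- **Section 2.4 (Blinding):** patients, health professionals, the research team and monitors all know the arm. Only the data analysis and the laboratories are blinded.
- **Section 5.2 (Study procedures):** the catheter is inserted after consent "and the inclusion and randomization of the participants".
- **Section 5.7 (Analysis plan):** "The analysis population will consist of all patients who meet the selection criteria and are randomized". It adds: "All patients included in the study and excluded from the analysis will be listed along with their reason for exclusion". Withdrawn patients are not replaced and missing data are not imputed.

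**The concern.** An eligibility criterion has to be decidable before allocation and has to be the same for every candidate. This one is neither: whether a patient who needs continuous drainage is eligible depends on the arm that patient draws.

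The definition of the analysis population carries the asymmetry into the results. Two identical patients, both needing continuous drainage, would be handled differently only because of their allocation: one fails the selection criteria and leaves the analysis set, the other meets them and stays. The Foley group would then contain a type of patient that the T-Control group does not.

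This touches the quantitative primary comparison (satisfaction and quality of life) and the comparative secondary endpoints on infection, antibiotic use, adverse events and cost. Blinding the analyst does not help, because the difference lies in who is in the data set.

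**Working it through.** **Step 1. What the study arm means.** Section 5.7 contrasts control and study groups, and the qualifier would say nothing if it covered both arms. It therefore means T-Control.

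**Step 2. Order of events.** Criteria are checked at the initial visit (2.2). Inclusion and randomisation follow, then insertion (5.2). The sequence is concealed (2.3). At the check nobody knows whether the candidate will be in the study arm, so exclusion 6 cannot be evaluated there as worded. It becomes decidable only after randomisation, when staff know the arm (2.4).

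**Step 3. The plan's own figure.** Section 5.3 gives d = 0.95, a 2.5% significance level, 5% dropout and 25 per group. Power and sidedness are not stated. With a two-sided t-test and an assumed power of 80%, n = 22.37, rounded up to 23; 23 / 0.95 = 24.2, rounded up to 25. The figure reproduces, so the sample size is not at issue.

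**Step 4. Bias formula.** Let q be the share of randomised patients needing continuous drainage, and g their mean outcome minus that of the other patients, in SD units (negative means worse). Assume no true treatment effect, and that all such patients leave the T-Control analysis set and none leave Foley. The expected means, relative to the other patients, are 0 in T-Control and q × g in Foley, so

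bias (T-Control minus Foley) = −q × g.

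**Step 5. False-positive rate for one questionnaire.** Normal approximation, two-sided 0.025 (critical value 2.241), starting from 25 per group before dropout:

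n_T = 25 × (1 − q); SE = √[1/n_T + (1 + q(1 − q)g²)/25]; rate = 1 − Φ(2.241 − bias/SE) + Φ(−2.241 − bias/SE).

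Example, q = 20% and g = −1: n_T = 20; SE = √(0.0500 + 0.0464) = 0.310; bias/SE = 0.20/0.310 = 0.644; rate = 0.057.

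The protocol gives neither q nor g. Both are assumed below.

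| q | n_T | g = −1.0: bias, rate | g = −0.5: bias, rate | g = 0: bias, rate | g = +0.5: bias, rate |
|---|---|---|---|---|---|
| 5% | 23.75 | +0.05, 2.7% | +0.025, 2.6% | 0, 2.5% | −0.025, 2.6% |
| 10% | 22.5 | +0.10, 3.3% | +0.05, 2.7% | 0, 2.5% | −0.05, 2.7% |
| 20% | 20 | +0.20, 5.7% | +0.10, 3.3% | 0, 2.5% | −0.10, 3.3% |

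A positive bias favours T-Control. The largest value in the table, 0.20 SD, is 0.20/0.95 = 21% of the planning effect; the smallest non-zero value, 0.025 SD, is 2.6% of it.

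The rates use the 2.5% level of section 5.3. Section 5.7 states a different p-value threshold (0.005), which is a separate matter; the bias itself does not depend on the level.

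**Step 6. After the fix.** With one rule applied to both arms before randomisation and everyone analysed as allocated, the bias from this source is 0 for any q and g, and 25 per group is unchanged.

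**The case against.** - **Staff may apply the criterion to everyone.** Any candidate might draw T-Control, so in practice all candidates needing continuous drainage could be screened out, with the qualifier only explaining why the rule exists. The bias would then be zero. This is a possible practice, but it contradicts the wording, which leaves such patients eligible for Foley.
- **No procedure removes the patient.** Need for continuous drainage is not among the reasons for discontinuing in section 5.2.1. That is correct, but the definition of the analysis population in section 5.7 is enough to remove the patient from the comparison.
- **Data are retained and exclusions are listed.** Section 5.6 says that collected data are kept and used, and sends early terminators to a substudy analysis; section 5.7 lists exclusions with reasons. A lopsided pattern would therefore be visible. Neither statement restores comparability or overrides the section 5.7 definition.
- **The share may be small.** Two criteria common to both arms, capacity to monitor the valve and no hourly output measurement, narrow the pool. This stands: q may be at or below the low end of the assumed range, where the false-positive rate barely moves.
- **This is a 50-patient pilot, and one primary endpoint is qualitative.** This also stands: the discussion groups are not a between-arm test and are not affected in this way.

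A reader might go further and infer that the trial is biased toward the sponsor's device, or that unblinded staff will use the rule selectively. The protocol supports neither. It does not say that patients needing continuous drainage have worse quality of life, more infections, more adverse events or higher costs. With g = 0 the bias vanishes, and with g positive it runs against T-Control. Nothing in the text describes selective use.

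**Conclusion.** The point holds as a design defect. The drainage exclusion is specific to one arm, cannot be decided at the stage where eligibility is checked, and, followed as written together with section 5.7, gives two analysis groups drawn from different populations. That conclusion rests on the text alone.

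The effect on the results cannot be determined from the protocol. Bias is possible; its sign follows g and its size follows q. In the scenarios where these patients fare worse, it is 0.025 to 0.20 SD toward T-Control, with a false-positive rate between about 2.5% and 6% for a nominal two-sided 2.5% test. The upper figures need both a 20% share and a full 1 SD deficit. The defect should still be corrected before analysis: patients missing from one arm's analysis set for this reason cannot be recovered by any comparison of those who remain.

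**What to change.** 1. Reconcile sections 2.2, 2.3, 4, 5.2 and 5.7 so that a single drainage-related eligibility rule applies identically to both arms. Its clinical content is for the sponsor to settle.
2. Assess that rule for every candidate and record the answer on the screening form before the randomisation system is accessed.
3. In section 5.7, define the primary analysis population as all randomised patients, analysed as allocated. The analysis of patients completing four weeks can stay as an additional analysis.

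The cost is a short amendment to the eligibility wording, the screening form and one sentence of the analysis plan. The eligible pool may change slightly, depending on the rule the sponsor adopts. The planned 25 per group does not change.

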T‐Control is a new silicone Foley catheter with an integrated valve to voluntarily control urine flow, which enables bladder filling and its conscious regulation and emptiness, thereby reducing mucosa irritation by contact of the catheter tip. This innovative valve controls urine flow by means of three different positions, from the proximal end of the tube. The “open” and “closed” positions regulate urine flow without other additional accessories required by the conventional Foley catheter. The third or “insertion” position, only available initially for the insertion manoeuvre, prevents unwanted urine leakage thanks to a specific built‐in membrane. T‐Control has an additional safety lock to prevent accidental opening of the catheter valve.

T‐Control has undergone and passed different biocompatibility studies, including the assessment of cytotoxicity, skin sensitization, intracutaneous reactivity (irritation), and acute, subacute, and subchronic systemic toxicity (necessary results to obtain the Conformité Europeéne marking). Beyond these preclinical biocompatibility studies, usability studies have also been performed to test the ease of professional handling of T‐Control. These confirm that an easier and safer insertion technique could be provided, while also being able to be performed by one person, which reduces the staffing needs currently recommended by clinical practice guidelines.^24^ Furthermore, patients' experience in the use of bladder catheters were comparatively evaluated with T‐Control and conventional catheters and recognized the added value and the intuitive and ease of use of T‐Control.^25^ Finally, in vitro studies have observed how T‐Control significantly prevented/delayed the formation and growth of biofilm during the first 5 days, compared with conventional Foley‐type catheter.^26^ In addition, another pilot clinical study is currently being carried out with the T‐Control catheter in patients with acute urinary retention (NCT05643950), for which the first results are expected to be obtained at the end of the first quarter of 2024.

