### Blinding

2.4

It will not be possible to blind the study arm for the trial subjects, the health professionals, the research team involved, and the monitoring team. Data analysis will be blinded to the intervention arm as well as the laboratories that will analyse the urine and catheter samples.

In the event of adverse events that may compromise the patient's safety, data may be unmasked by means of the unique code given to each participant.

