##### Number of adverse events related to catheterization

The type and number of adverse events will be registered in the Patient's Clinical Data Notebook: accidental disconnection of the catheter, obstruction, pain, loss of urine per catheter, haematuria, and accidental spills caused by the professional during insertion. The patient will receive a Patient Incident Diary to write down the incidents, along with other information that may be of interest during catheterization. Timing and source of adverse events data are summarized in Table 1.

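### Exclusion criterion 7 (more than one insertion attempt) can be judged only after randomisation, yet the analysis population is restricted to randomised patients who meet the criteria

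*Protocol article*

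**What the plan says.** Section 4 (Eligibility criteria) gives as exclusion criterion 7 "catheter insertion requiring more than one attempt".

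Section 2.2 (Recruitment) describes an initial visit "where the inclusion and exclusion criteria will be checked". Section 5.2 (Study procedures) then fixes the order: "The catheter will be inserted by the research staff after obtaining informed consent (Data S8), and the inclusion and randomization of the participants".

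Section 5.7 (Analysis plan) defines the main population: "The analysis population will consist of all patients who meet the selection criteria and are randomized". It adds that "All patients included in the study and excluded from the analysis will be listed along with their reason for exclusion". Section 5.6 (Oversight and monitoring), by contrast, says that all data collected are kept and used, that early terminators go into a substudy analysis, and that deviations are recorded.

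Three further statements bear on the point. The Background reports usability work suggesting that with T-Control "an easier and safer insertion technique could be provided". Section 2.4 (Blinding) says "It will not be possible to blind the study arm for the trial subjects, the health professionals". Section 5.4.2 includes among the adverse events "accidental spills caused by the professional during insertion".

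**The concern.** A criterion that is resolved only when the allocated catheter goes in is not a baseline characteristic. It is an early result of the treatment received. Used to define who is analysed, it makes the comparison conditional on something that allocation may have changed, and the retained groups are then no longer protected by randomisation. Blinded data analysis does not repair this, because the selection has already happened.

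Two features make the selection potentially unequal between arms. The article itself expects the device to matter at insertion. And what counts as a second attempt is decided by professionals who know the arm and who, under section 2.3, also enter patients on the randomisation system.

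The outcome most exposed is adverse events at insertion, whose comparison is part of a secondary objective: a patient whose first attempt fails is a plausible candidate for such an event. The primary comparison of satisfaction and quality of life would also be made in a selected set.

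**Working it through.** **1. Can the criterion be assessed before allocation?**

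| Step | Section | Is the number of attempts with the study catheter known? |
|---|---|---|
| Criteria checked at initial visit | 2.2 | No |
| Consent, inclusion, randomisation | 2.3, 5.2 | No |
| Insertion of allocated catheter | 5.2 | Yes, for the first time |
| Analysis set: randomised and meeting criteria | 5.7 | Used to include or exclude |

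Section 5.2.1 does not list repeated attempts as a reason for discontinuation. The only route by which such a patient leaves the comparison is therefore section 4 read with section 5.7, and section 5.6 pulls the other way.

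**2. The plan's own sample size (section 5.3).** Inputs: standardised difference d = 0.95, significance level 0.025, 5% dropout, 25 per group. Power and sidedness are not stated; I assume 80% and two-sided.

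- Normal approximation: n = 2(z₀.₉₈₇₅ + z₀.₈₀)²/d² = 2(2.241 + 0.842)²/0.9025 ≈ 21.1, so 22; 22/0.95 = 23.2, so 24.
- Exact t-test: 23; 23/0.95 = 24.2, so 25.

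The stated 25 per group reproduces, so the sample-size arithmetic is not at fault.

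**3. Power if criterion 7 removes patients.** Let q be the proportion excluded. The article gives none, so every q is an assumption. Evaluable n per arm = 25 × 0.95 × (1 − q); power is from the two-sided t-test at 0.025 with d = 0.95.

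| q in both arms | n per arm | Power |
|---|---|---|
| 0 | 23.75 | 0.827 |
| 5% | 22.6 | 0.804 |
| 10% | 21.4 | 0.779 |
| 20% | 19.0 | 0.720 |

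With unequal rates of 5% and 20% (22.6 and 19.0 patients), power is 0.762. These figures also assume that excluded patients are not replaced, which the article does not say.

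**4. How large could the bias be?** Suppose there is no true device effect. In both arms a share p_C of patients is hard to catheterise, and these patients score D standard deviations lower. The Foley arm excludes all of them. The T-Control arm excludes a smaller share p_T of its patients, all from the hard group. The Foley mean is then 0, and the hard patients left in the T-Control arm pull its mean down:

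spurious difference (T-Control − Foley) = −D × (p_C − p_T)/(1 − p_T)

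| p_T / p_C | D = 0.5 | D = 1 |
|---|---|---|
| 5% / 10% | −0.03 | −0.05 |
| 5% / 20% | −0.08 | −0.16 |
| 0% / 20% | −0.10 | −0.20 |

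For example, 0.15/0.95 = 0.158 with D = 1. The sign reverses if T-Control loses more patients. All inputs are assumed; the table shows scale, not an estimate.

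**The case against.** **Removal is inferred.** No sentence says that a patient needing a second attempt is withdrawn, and the criterion might be meant as a history of difficult catheterisation, since these patients already carry a catheter. The wording does not say so, however, and if that was the intention it still needs correcting. What stands is that sections 5.6 and 5.7 conflict. It would go too far to say that the data will certainly be discarded.

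**A reader might infer that the exclusions disappear without trace.** They do not: section 5.7 lists excluded patients with reasons, so an imbalance between arms would be visible. Visibility does not remove the bias.

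**A reader might infer that excluded patients are not replaced.** Section 5.7 says this only of subjects who withdraw. The power figures rest on extending that rule and should carry little weight.

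**A reader might infer that T-Control is known to change the number of attempts, or that insertion events are bound to be undercounted.** Neither is shown. The Background statement concerns ease of handling and insertion by one person. In section 5.4.2 only spills are tied to insertion; pain and haematuria are listed generally. Table 1 records insertion events by observation at baseline, so an event at a failed attempt can be captured. Whether it is then analysed depends on the unresolved text.

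**The scale may be small.** This is a 50-patient pilot, and urinary tract malformations and urological cancer are already excluded, so 20% may be high. The illustrated biases are well below the planned 0.95. That is fair for the quality-of-life endpoint. It reassures less for insertion events, which occur at the very step on which patients are selected.

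**Conclusion.** The point holds as a defect in how eligibility and the analysis population fit together. Following sections 4, 5.2 and 5.7 as written conditions the main comparison on a post-randomisation event, recorded by unblinded staff and plausibly related to the device. This is not a matter left to the SAP, because the article itself fixes both the criterion and the population.

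The direction and size of the bias cannot be determined from the article. The illustration gives up to 0.2 standard deviations, and only with a large difference in exclusion rates between arms and markedly worse scores in the excluded patients. The effect on power is modest at exclusion rates of 5% to 10% and is not the reason to act. The reason is that the randomised comparison can be kept intact at almost no cost.

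**What to change.** - In section 5.7, define the primary analysis population as all randomised patients, analysed by allocated arm, regardless of the number of insertion attempts.
- Record the number of attempts for each patient and report it by arm as an insertion outcome.
- Present single-attempt patients only as a sensitivity analysis.
- Reconcile sections 4, 5.2, 5.6 and 5.7, so that any eligibility criterion on insertion difficulty can be assessed before randomisation. Whether to keep such a criterion, and in what form, is for the sponsor to decide.
- State that 4-week data are still collected from randomised patients who needed more than one attempt. Section 5.7 allows no imputation, so without those data the wider population would exist only on paper.

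The cost is a change of wording in eligibility and analysis population and one case report form field. The drawback is slightly more noise from multi-attempt patients.
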